### Statistical analysis plan

All statistical analyses will be performed using SAS version 9.1 or a later version. All statistical tests will be two-sided and the level of significance will be set at 0.05. The last observation carried forward (LOCF) method will be used to input data with dropouts. Continuous variables will be expressed as mean ± SD, and categorical variables as number and percentage.

The primary endpoint will be compared in the four groups by analysis of covariance (ANCOVA),with treatment means adjusted to baseline WOMAC scores as a covariate. Confidence intervals will be derived from ANCOVA. Repeated measures analysis of variance (ANOVA) will also be used to analyze primary and secondary efficacy variables. Categorical data will be analyzed using Pearson’s chi-square test or Fisher’s exact test.

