### Analysis of data

The primary efficacy endpoint of the study will be the change in Western Ontario and McMaster Universities Osteoarthritis Index (WOMAC) [31] score from before to after the 6-week, 12-visit trial.

The WOMAC is a widely used, reliable, valid and responsive measure of treatment outcomes in patients with OA of the hip or knee [31]. The WOMAC index consists of 24 questions (5 related to the amount of pain, 2 to stiffness and 17 to physical function), and takes less than 5 minutes to complete [32]. The Likert version of the WOMAC rates each question on an ordinal scale of 0 to 4, with lower scores indicating lower levels of symptoms or physical disability [33].

Secondary efficacy endpoints will include: 1. the success rate of treatment; 2. change in scores on the WOMAC pain subscales; 3. 100 mm pain VAS on walking; 4. results of a 6-minute walk test; and 5.investigator global assessment (IGA)/patient global assessment (PGA). Treatment success will be defined as ≥36% improvement in WOMAC score, and treatment failure by a change <36% in WOMAC score or a missing value [34].The 100 mm pain VAS on walking is used to evaluate the severity of pain. The patient will be asked to walk 15 m in a straight line and to determine his/her level of pain from 0 mm (absence of pain) to 100 mm (worst pain imaginable).The 6-minute walk test, which measures the distance a person can walk in 6 minutes, has been found to reliably measure functional exercise capacity and has been frequently used in OA-related trials [35,36]. For IGA and PGA, the oriental medicine doctor and the patient, respectively, will evaluate general improvements in OA pain-related symptoms, using a five-grade scale: excellent, good, fair, poor and aggravated. The 100 mm VAS on walking, WOMAC pain scale and IGA/PGA will be assessed at baseline, at each treatment session, and 12 weeks after the start of treatment. The WOMAC and 6-minute walk tests will be assessed at baseline, and after 3, 6 and 12 weeks from the start of the trial.

In addition, the patients will be asked to record their symptoms according to a VAS each morning and evening during the duration of the trial. They will also be asked to record the medications they take, such as analgesics and NSAIDs for knee pain, at the beginning of the trial, at each treatment session, at the end of treatment (week 6), and at 12 weeks after the start of the treatment (Table 2).

**Table 2 T2:** Example of outcome measurements

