**Measures**		**Treatment visit**												
	**Baseline**	**1**	**2**	**3**	**4**	**5**	**6**	**7**	**8**	**9**	**10**	**11**	**12**	**Follow-up**
*Primary outcome measure*														
WOMAC^a^	x							x					x	x
*Secondary outcome measure*														
Success rate^b^	x							x					x	x
WOMAC pain(subscale)	x	x	x	x	x	x	x	x	x	x	x	x	x	x
100 mm pain VAS on walking	x	x	x	x	x	x	x	x	x	x	x	x	x	x
6-minute walk test	x							x					x	x
IGA/PGA	x	x	x	x	x	x	x	x	x	x	x	x	x	x

^a^The primary outcome is the change of WOMAC score after the 12-visit, 6-week trial.^b^Success will be defined as ≥36 % improvement in WOMAC score, and failure as <36 % improvement or missing values.IGA, investigator global assessment; PGA, patient global assessment; VAS, visual analogue scale; WOMAC, Western Ontario and McMaster Universities Osteoarthritis Index.

Any reported adverse events will be recorded throughout the study, and vital signs will be monitored at each visit.

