### Sample size

The primary efficacy parameter is change in WOMAC score from baseline to the end of treatment after 6 weeks. The standard deviation (SD) of the WOMAC score is 3.35 [27]. In calculating the appropriate sample size for this study, we sought to obtain a more conservative SD, with a true mean difference of 2.34.

With *μ*_1_ and *μ*_2_ representing the mean WOMAC scores for the test and control groups, respectively, the null-hypothesis 

$$H_{0}:\mu_{1}-\mu_{2}=0$$

 will be tested versus the alternative hypothesis 

$$H_{1}:\mu_{1}-\mu_{2}\neq 0$$

Using these hypotheses, we calculated the sample size needed to achieve 80% power using the equation: 

n=Zα/2+Zβ2σ2μ1-μ22.

To show that the individualized treatment group is not equal to the control groups, patients will be randomized 2:2:1:1 to the individualized treatment group, standard treatment group, sham group and untreated group, respectively. Using these assumptions and specifications, a sample size of 198 individuals (66:66:33:33) will provide a power of 80% at a significance level of 0.05. To allow for a 20% dropout rate, a slightly higher number, 250 patients, will be randomized in the trial.

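### LOCF is the only dropout rule for the week-6 WOMAC endpoint and can bias the contrast, with size and sign unknown; its precedence over missing = failure for treatment success is not stated.

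*Protocol article*

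**What the plan says.** The Statistical analysis plan section of the protocol article states: "The last observation carried forward (LOCF) method will be used to input data with dropouts". It excepts no endpoint and names no alternative or sensitivity analysis. The primary comparison is an ANCOVA across the four groups, adjusted for baseline WOMAC. A supporting analysis is added: "Repeated measures analysis of variance (ANOVA) will also be used to analyze primary and secondary efficacy variables".

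The Sample size section defines the endpoint, "The primary efficacy parameter is change in WOMAC score from baseline to the end of treatment after 6 weeks", and sets the expected loss: "To allow for a 20% dropout rate, a slightly higher number, 250 patients, will be randomized in the trial". It gives no split by arm and no timing.

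The Analysis of data section gives the schedule: "The WOMAC and 6-minute walk tests will be assessed at baseline, and after 3, 6 and 12 weeks from the start of the trial". Table 2 agrees, with total WOMAC at baseline, visit 7, visit 12 and follow-up. Only the WOMAC pain subscale is taken at every session.

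For the secondary endpoint of treatment success, the same section defines "treatment failure by a change <36% in WOMAC score or a missing value". The footnote to Table 2 repeats it: "failure as <36 % improvement or missing values".

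**The concern.** Up to week 6, LOCF has only two values to carry. A patient who leaves before week 3 is given the baseline score, that is, a change of zero. One who leaves between weeks 3 and 6 is given a score from halfway through treatment. The ANCOVA then treats both as observed week-6 results, and on the plan's own allowance this may apply to up to a fifth of patients.

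That is harmless only in special cases, for example if nobody leaves before week 3 and week 3 already shows the whole effect. The article's own reason for a 6-week course, a survey in which 50.6% of practitioners thought more than 5 weeks necessary, argues against such a case.

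Equal dropout cannot be taken for granted either. Patients in the untreated arm get no needling and know it, yet are assessed at each visit. At stake are the size of the primary estimate and, if dropout is unequal, the error rate of its test.

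The second strand is smaller. Success is derived from the same WOMAC score. If LOCF is applied first, no dropout has a missing score, and the missing = failure rule no longer acts on dropouts.

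**Working it through.** **1. The plan's own figures.** With SD 3.35, difference 2.34, two-sided 5% and 80% power, n per arm = 2 × (1.960 + 0.842)² × 3.35² / 2.34² = 32.2, rounded up to 33. Taking 33 as the smallest arm at 2:2:1:1 gives 6 × 33 = 198, as stated. Dividing by 0.8 gives 247.5, against 250 stated. So 20% dropout is the plan's own working figure. At 250 patients a larger arm has about 83 and a smaller arm about 42.

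**2. What LOCF does to the contrast.** Assumptions not in the documents:
- b = share of dropouts who leave before the week-3 WOMAC
- r = share of the week-6 improvement reached by week 3
- m = improvement in the control arm
- dropout unrelated to a patient's own course

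With dropout d, an arm's mean improvement is multiplied by (1 − d) + d(1 − b)r = 1 − kd, where k = 1 − (1 − b)r. For true difference δ, active dropout dA and control dropout dC:

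bias = k × [m(dC − dA) − δ·dA]

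The bias favours acupuncture only if m(dC − dA) exceeds δ·dA.

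**3. Equal dropout, 20%/20%, δ = 2.34.** The result does not depend on m.
- All dropouts carry baseline (k = 1): 2.34 × 0.80 = 1.87.
- b = r = 0.5 (k = 0.75): 2.34 × 0.85 = 1.99.
- All leave after week 3 with the full effect already present (k = 0): 2.34, no bias.

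**4. Unequal dropout, δ = 2.34, b = r = 0.5.**

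| Dropout, active/control | m = 2 | m = 4 |
|---|---|---|
| 15%/25% | 2.23 | 2.38 |
| 10%/30% | 2.46 | 2.76 |
| 30%/10% | 1.51 | 1.21 |

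At 15%/25% the sign turns at m = 2.34 × 0.15 / 0.10 = 3.5 points.

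**5. No true effect.** The LOCF contrast is k·m(dC − dA). With 83 v 42 patients, SD 3.35 and no allowance for covariate adjustment, SE = 3.35 × √(1/83 + 1/42) = 0.634. With b = r = 0.5:

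| Dropout, active/control | m = 2 | m = 4 | m = 6 |
|---|---|---|---|
| 20%/20% | 5.0% | 5.0% | 5.0% |
| 15%/25% | 5.6% | 7.6% | 10.9% |
| 10%/30% | 7.6% | 15.7% | 29.5% |

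For example, at m = 4 and 10%/30% the spurious contrast is 0.75 × 4 × 0.20 = 0.60, or 0.95 SE, giving 15.7%.

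**6. Dependence on scale.** Type I error depends on natural improvement relative to the SD. With an assumed SD of 15, m = 6, b = 0.4 and r = 0.5 (k = 0.7), the null contrast at 10%/30% is 0.7 × 6 × 0.20 = 0.84. The SE is 2.84 and the type I error 6.0%. With a true difference of 9 in that setting, LOCF gives 7.7 at 20%/20%, 8.5 at 15%/25%, 9.2 at 10%/30% and 6.3 at 30%/10%.

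**7. Treatment success.** The two rules differ only for a patient who improved by at least 36% at week 3 and then left: a success under LOCF, a failure under the endpoint definition. The gap in an arm is d × (share of dropouts leaving after week 3) × (share of those who met the cut at week 3). With d = 0.20 it runs from 0.20 × 0.5 × 0.2 = 2 points to 0.20 × 1.0 × 0.4 = 8 points. The last two factors are assumed.

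**The case against.** Four stronger readings are tempting, and the documents do not support them.

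- **LOCF will favour acupuncture if controls leave more often.** Not in general. At 15%/25% with m = 2 the estimate is still below the truth. If active patients leave more often the shrinkage is large (1.21 to 1.51 against 2.34).
- **The two missing-data rules contradict each other.** Missing = failure is part of the definition of one secondary responder endpoint and is stated twice. The ordinary reading lets a specific definition override a general sentence, and a continuous and a responder endpoint may properly have different rules. What remains is an overlap with no stated precedence. A SAP not shown may settle it.
- **The repeated-measures ANOVA is a further defect.** The ANCOVA carries the primary comparison and the ANOVA is an addition. A supporting analysis need not target week 6.
- **Every contrast is exposed to unequal dropout.** The reason offered concerns the untreated arm. Individualized, standard and sham patients follow the same visit schedule and are blinded to which needling they receive; nothing in the article suggests unequal loss among them.

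It is also fair to say that the sizes rest on assumptions: neither timing nor balance of dropout is given, and the null test holds its level when dropout is equal. None of this rescues LOCF as the sole method. The article fixes it expressly, so the point is not about detail left to a SAP.

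**Conclusion.** The concern holds in qualified form. LOCF as the only dropout rule is a weak choice for this endpoint because it can carry only a baseline or a week-3 score to week 6, with 20% dropout planned. It can bias the primary contrast; that it will, in which direction and by how much cannot be read from the documents.

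On the plan's SD and difference, with half the dropouts before week 3 and half the effect by then, a true 2.34 becomes about 2.0 at equal 20% dropout. With no true effect and 4 points of natural improvement, type I error is about 5% at 20%/20%, 8% at 15%/25% and 16% at 10%/30%. These figures illustrate the problem and are not forecasts: with natural improvement small relative to the SD, the last falls to about 6%.

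The success-rate overlap is a minor ambiguity in a secondary endpoint, worth a few percentage points per arm. The plan should be changed, but the trial is not invalidated.

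**What to change.** For the primary endpoint, replace LOCF by one of the following, with site included and WOMAC at weeks 3, 6 and 12 used:

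- A likelihood-based repeated-measures model with the week-6 contrast as the primary estimate. Put baseline WOMAC in the response vector, with its mean constrained equal across arms. If baseline is only a covariate, a patient with no later WOMAC drops out of the likelihood. At 20% dropout with half leaving before week 3, that is about 25 of 250 patients.
- Multiple imputation, followed by the planned ANCOVA.

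Keep LOCF at most as a sensitivity analysis. Add one sentence saying that treatment success is derived from observed WOMAC with missing = failure and is exempt from LOCF.

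The cost is reliance on a missing-at-random assumption and slightly more analysis work. No new data are needed. The article reports that enrolment was still under way, so the wording could have been changed before results were known.

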## Discussion

The individualized acupuncture treatment method proposed in this study, consisting of meridian-based syndrome differentiation and Sa-am acupuncture, is not only the most commonly method used by certified oriental medicine doctors in Korea to treat patients with OA [21,25], but can be generalized for widespread use in the future. In this trial, we will evaluate the efficacy of this individualized treatment method by comparing it with standard, sham and non-treatment groups.

The acupuncture methods employed in this study are the closest to actual clinical practice and can be used in future studies. Moreover, the techniques of meridian based and Sa-am acupuncture that we will use in this study are based on the consensus of many certified oriental medicine doctors in Korea. In addition, we will strive to conduct a high quality, single-blinded clinical trial by ensuring that the assessors and participants are not informed of the type of treatment, by using a variety of controls including Park sham acupuncture, and providing trial-specific training of the exact methods used to well-qualified and certified oriental medicine doctors.

In conclusion, this research involves three different controls, and it will help elucidate the efficacy of individualized acupuncture versus standard, sham and no acupuncture groups.

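### The four-group ANCOVA fixed as the primary analysis matches neither the two-group hypothesis used for sizing nor the aim of individualized acupuncture versus three controls

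*Protocol article*

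**What the plan says.** All the relevant text is in the protocol article.

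- **Sample size, hypothesis.** There is one null hypothesis, that the difference between two means is zero, the means "representing the mean WOMAC scores for the test and control groups, respectively, the null-hypothesis" being tested against a two-sided alternative.
- **Sample size, purpose of the allocation.** The 2:2:1:1 ratio is introduced with the words "To show that the individualized treatment group is not equal to the control groups", in the plural. The resulting size is 66:66:33:33, or 198 evaluable patients, for 80% power at 0.05. To allow for 20% dropout, 250 are randomized.
- **Discussion.** The comparisons of interest are listed: "we will evaluate the efficacy of this individualized treatment method by comparing it with standard, sham and non-treatment groups".
- **Statistical analysis plan.** The primary analysis is given as "The primary endpoint will be compared in the four groups by analysis of covariance", with the baseline WOMAC score as covariate. The next sentence is "Confidence intervals will be derived from ANCOVA". The error rate is set by "All statistical tests will be two-sided and the level of significance will be set at 0.05".

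The article names no primary contrast, order of testing, multiplicity adjustment or rule for success. It also does not say that unadjusted pairwise tests will be run.

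**The concern.** The sizing hypothesis concerns one difference, the aim concerns three differences, and the primary analysis as worded concerns equality of four means. A significant comparison of four means shows that some arm differs from some other. It does not show that individualized acupuncture differs from any particular control.

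This matters because of the fourth arm. Patients there receive no needling and so know it, and the primary endpoint is a self-reported score. Of the four arms it is the most likely to differ for non-specific reasons. A difference confined to that arm says nothing about whether individualization adds anything over standard or sham needling, which is the trial's question.

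Moving to the three contrasts does not settle the matter if each is tested at 0.05 without a rule for combining them. The investigators could then claim success against whichever control reaches significance.

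**Working it through.** **Inputs.** From Sample size: SD 3.35 ("The standard deviation (SD) of the WOMAC score is 3.35"), difference 2.34, two-sided alpha 0.05, power 80%, evaluable arms 66:66:33:33 (individualized, standard, sham, none). Standardized difference: 2.34 / 3.35 = 0.6985.

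**1. The plan's own figure.** For two equal groups, n per group = 2 × (1.960 + 0.842)² × 3.35² / 2.34² = 32.17, rounded up to 33. Doubling two arms gives 66 + 66 + 33 + 33 = 198. With 20% dropout, 198 / 0.8 = 247.5, so 248, and 250 is in line. The stated size reproduces as a single two-group comparison at 0.05.

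**2. The four-group test as the basis for the conclusion.** Suppose individualized = standard = sham, and only the untreated arm is worse, by 0.6985 SD.
- Noncentrality = 33 × 0.6985² × (1 − 33/198) = 13.42.
- With 3 and 193 degrees of freedom (198 patients less four means and one covariate), the chance of significance at 0.05 is 0.875. A simulation of 1,000,000 trials also gave 0.875.

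This is a correct rejection of equality of four means. It becomes an error only if read as efficacy over sham or standard.

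**3. Three contrasts, each at 0.05, any one counting.**
- Correlation of individualized-minus-standard with either other contrast: (1/66) / √[(2/66)(3/66)] = 0.408.
- Correlation of the sham and untreated contrasts: (1/66) / (3/66) = 0.333.
- With all four arms equal, the trivariate normal probability that at least one exceeds 1.96 in absolute value is 13.2% (simulation 13.2%). Treated as independent it would be 1 − 0.95³ = 14.3%.
- At about 83:83:42:42, close to the randomized numbers, it is again 13.2%.

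**4. The same contrasts, looked at only if the four-group test is significant (simulation).**
- All arms equal: at least one false claim in 4.3%.
- Only the untreated arm differs, by 0.6985 SD: a false claim versus standard or sham in 9.1%. The gate is usually open in that case and gives little protection.
- Holm adjustment of the three contrasts in that same case: 4.3%.

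**5. Power per contrast after adjustment.** Power ≈ Φ(0.6985 / √(1/n₁ + 1/n₂) − z), with z = 1.960 at 0.05 and 2.394 at 0.05/3.

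| Contrast | Standardized shift | Power at 0.05 | Power at 0.05/3 |
|---|---|---|---|
| 66 vs 33 (sham or none) | 3.276 | 90.6% | 81.1% |
| 66 vs 66 (standard) | 4.013 | 98.0% | 94.7% |

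Using the t distribution instead lowers the last column slightly, to about 80.5% and 94.4%. A Dunnett-type critical value is about 2.37 (per-test alpha about 0.018), slightly less strict than Bonferroni.

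**The case against.** The strongest reply is that the article names a model, not a decision rule. ANCOVA on four groups can yield adjusted pairwise differences, and the sentence on confidence intervals fits estimates from the model better than an F-test. Sample size says a two-group null will be tested. On that reading the plan already intends individualized-versus-control comparisons from the ANCOVA, and their order and adjustment may stand in a full protocol or SAP that is not shown. This stands to the extent that silence on adjustment is not itself a fault in an article.

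It follows that two stronger readings, which a reader might infer, are not supported:

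- **That the plan runs at a 13% error rate.** This needs three unadjusted, ungated tests with any one counting as success, and the article states no such procedure. If the claim required significance against all three controls, which the plural wording in Sample size permits, each test at 0.05 would need no adjustment.
- **That an omnibus F-test is the stated rule for success, with an 87% false-positive rate.** No F-test is named, and in that scenario the arms do differ. The 87% and the 13% also belong to different readings and cannot both describe the plan.

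Nor can an intended adjustment be read into the sample size. It happens that 66 versus 33 is also what 0.05/3 at 2:1 requires, but the article states 0.05.

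What the reply does not remove is the conflict in the text that is there. The section headed as the statistical analysis plan fixes a four-group comparison and 0.05 for all tests, beside a two-group hypothesis and a three-control aim.

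**Conclusion.** The mismatch is real: the primary analysis as stated corresponds neither to the hypothesis on which the trial was sized nor to its aim. The consequence depends on how the text is applied:

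- **Conclusion drawn from the four-group test:** significant in about 87% of trials in which individualized equals standard and sham and only the untreated arm differs.
- **Three contrasts at 0.05, any one sufficient:** family-wise error about 13% with all arms equal.
- **Contrasts gated by the four-group test:** about 4% with all arms equal, but about 9% for a false claim versus standard or sham when only the untreated arm differs.
- **All three contrasts required:** no inflation, but this rule is not stated.

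The figures rest on 66:66:33:33, a common SD, normal theory and, for the scenarios with a difference, an untreated arm worse by the planned 2.34. They describe possible uses of the wording, not a procedure that the article commits to. Because the readings lead to such different conclusions, the text should be corrected before the data are analyzed.

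**What to change.** Name the individualized-versus-control contrasts (minus standard, minus sham, minus no acupuncture), estimated from the same baseline-adjusted ANCOVA, as the primary analysis, and state one decision rule:

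- Holm or Dunnett adjustment, with strong family-wise control at 0.05;
- a fixed sequence of the contrasts, set in advance; or
- significance against all three controls required, each at 0.05 without adjustment.

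State also that the conclusion will not rest on the four-group test and that a claim of efficacy over sham requires the sham contrast itself. Rewrite the hypothesis in Sample size to match. Any of the three rules would serve, and the choice is the sponsor's. Enrollment was still under way at publication.

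**Cost.** The change is to wording and needs no extra patients. With adjustment, the per-contrast threshold becomes stricter. At 0.05/3, power is about 80 to 81% for 66 versus 33 and about 94% for 66 versus 66, so the stated 80% is kept for each contrast. This assumes that 2.34/3.35 applies to every contrast. The article gives no separate justification of that difference for individualized versus standard, where both arms receive active electroacupuncture. Power to succeed on all three contrasts is lower than any of these figures, which should be acknowledged if the all-three rule is chosen.

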## Methods/Design

### Study design

This prospective parallel, single-blinded (assessor and patient), randomized controlled trial (RCT) is designed to assess the efficacy and safety of individualized acupuncture therapy in patients with knee OA. It will be conducted at two clinical research centers in South Korea, Semyung University Oriental Medicine Hospital in Chung-ju and Dongguk University Oriental Hospital in Ilsan, with patients divided into four parallel groups. The research protocol has been approved by the institutional review board (IRB) at each center, and each patient will be asked to provide informed consent.

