### Randomization and blinding

Patients will be randomized by an independent statistician using a computerized, random-number generator through the block-randomization method of SAS version 9.1(SAS Institute Inc, Cary, NC, USA) for sequence generation. Separate randomization files will be created for each of the two sites. Allocations will be concealed using sealed, opaque envelopes. After the assessor has screened the patient for inclusion and the patient has signed the informed consent form, the next envelope in the sequence will be provided, immediately prior to treatment, to the certified oriental medicine doctor who will perform acupuncture. By this method, a total of 250 participants will be randomly assigned to the four groups. Although all patients and their screening assessors will be blinded to treatment, the certified oriental medicine doctor applying acupuncture will not.

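### Allocation is listed separately by hospital, but the stated primary ANCOVA names only baseline WOMAC; to the extent the hospitals differ, its standard error is too large

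*Protocol article*

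**What the plan says.** Under Study design, the article says of the trial: "It will be conducted at two clinical research centers in South Korea". Under Randomization and blinding, the sequence comes from the "block-randomization method of SAS version 9.1", and "Separate randomization files will be created for each of the two sites". Hospital is therefore a stratification factor, and allocation is balanced within each hospital by design.

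Under Statistical analysis plan, the four groups are compared on the primary endpoint by ANCOVA, with "treatment means adjusted to baseline WOMAC scores as a covariate". The same model supplies the intervals: "Confidence intervals will be derived from ANCOVA". On error rates, "All statistical tests will be two-sided and the level of significance will be set at 0.05". Neither this section nor any other names hospital as a term in an analysis.

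**The concern.** When allocation is balanced within hospital, a difference in average response between hospitals cancels out of the treatment contrast. The estimate therefore varies from trial to trial only with the within-hospital variance. A model without hospital does not know this. It puts the between-hospital variance into the residual and reports a standard error larger than the estimate's true sampling SD. Intervals then cover more than their nominal 95%, the test rejects less often than 5% under the null, and some of the precision obtained by stratifying is not used.

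What is at stake is precision, and agreement between the analysis and the design. The validity of a positive result is not at stake.

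**Working it through.** **Inputs from the Protocol article.** Two hospitals with separate block-randomised lists (Study design; Randomization and blinding). Two-sided 0.05 (Statistical analysis plan). SD 3.35, difference 2.34, 80% power, 198 evaluable patients as 66:66:33:33, 20% dropout, 250 randomised (Sample size).

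**Assumed input.** ρ is the share of residual variance, after baseline adjustment, that is due to hospital. The article gives no value, so a range of 0 to 0.20 is used.

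**Step 1: reproduce the plan's figures.** For two equal arms, n = 2(1.960 + 0.842)² × 3.35² / 2.34² = 2 × 7.85 × 11.22 / 5.476 ≈ 32.2, so 33 per arm. Taking 33 as the smaller arm gives 66:66:33:33 = 198. Allowing for dropout, 198 / 0.8 = 247.5, so 248, close to the stated 250. The stated 80% is thus the power of a 33 v 33 comparison (0.81 at n = 33).

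**Step 2: power of the comparison actually made.** For individualized against sham or untreated, 66 v 33, SE = 3.35 × √(1/66 + 1/33) = 0.714. Power = Φ(2.34/0.714 − 1.96) = Φ(1.316) = 0.906.

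**Step 3: effect of leaving site out.** Take 3.35 as the total residual SD, including any site variance.
- SE ratio (site omitted / site included): f = 1/√(1 − ρ)
- True type I error without site: 2[1 − Φ(1.96 f)]
- Power without site: Φ(2.34/SE_true − 1.96 f), where SE_true = 0.714 √(1 − ρ)
- Power with site: Φ(2.34/SE_true − 1.96)
- Implied gap between two equal-sized hospitals: 2√ρ × 3.35 points

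| ρ | Implied gap (points) | SE ratio | Type I error, no site | Power, no site | Power, with site |
|---|---|---|---|---|---|
| 0 | 0 | 1.000 | 0.050 | 0.906 | 0.906 |
| 0.02 | 0.95 | 1.010 | 0.048 | 0.908 | 0.911 |
| 0.05 | 1.50 | 1.026 | 0.044 | 0.912 | 0.919 |
| 0.10 | 2.12 | 1.054 | 0.039 | 0.917 | 0.932 |
| 0.20 | 3.00 | 1.118 | 0.028 | 0.929 | 0.956 |

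Worked line for ρ = 0.10: SE_true = 0.714 × √0.9 = 0.678 and 2.34/0.678 = 3.453. Without site, Φ(3.453 − 2.066) = 0.917; with site, Φ(3.453 − 1.960) = 0.932.

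**Step 4: simulation under the null** (4,000 trials per scenario, two hospitals of 99, 2:2:1:1, the 33 v 66 contrast).

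| ρ | Model | Mean reported SE | Actual SD of estimate | Rejection rate |
|---|---|---|---|---|
| 0 | no site | 0.714 | 0.724 | 5.5% |
| 0 | site | 0.714 | 0.724 | 5.5% |
| 0.10 | no site | 0.716 | 0.683 | 3.7% |
| 0.10 | site | 0.678 | 0.683 | 5.0% |
| 0.20 | no site | 0.716 | 0.637 | 2.6% |
| 0.20 | site | 0.640 | 0.636 | 4.5% |

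The Monte Carlo standard error of a 5% rate is √(0.05 × 0.95/4000) ≈ 0.3 points, so the scatter around 5% in the site-adjusted rows is unremarkable. The pattern agrees with Step 3: without site, the reported SE exceeds the actual SD once ρ is above zero. When ρ is zero, adding site makes no visible difference.

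**Step 5: sensitivity to the meaning of 3.35.** If 3.35 is instead the within-hospital SD and two equal hospitals differ by D of those SDs, the SE ratio is √(1 + D²/4). That gives 1.031 at D = 0.5 and 1.118 at D = 1. Power for 66 v 33 without site is Φ(3.276 − 1.96 × 1.031) = 0.895 and Φ(3.276 − 1.96 × 1.118) = 0.861, against 0.906 with site.

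**The case against.** Several points on the other side have force.

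- **The loss is conditional.** It is zero if hospital does not predict WOMAC change after baseline adjustment, and the article gives no between-hospital figure. A reader might infer that a difference is likely because practitioners differ. The article does not show this. Quality assurance describes steps towards uniformity: common qualifications, a two-day workshop, written protocols and restricted doctor–patient interaction. Practitioner differences would also act mainly in the needled arms, which is a site-by-treatment interaction that an additive site term does not model. This objection stands, and the point must be put conditionally.
- **The top of the range is extreme.** At ρ = 0.20 equal hospitals would differ by 3.0 points, more than the 2.34 treatment difference being planned for. Nothing in the article supports a gap of that size. For a given gap, an equal split between hospitals is also the worst case, and the split is not stated.
- **Power.** A reader might take the statement that the sample "will provide a power of 80% at a significance level of 0.05" and infer a fall from 80% to about 78% or 73% (D = 0.5 or 1). That starts from the 33 v 33 calculation. The comparison made is 66 v 33, with power near 0.91. If 3.35 is a total SD, power without site does not fall below that figure; only a possible gain is forgone.
- **Validity.** A reader might infer biased estimates or false positives. Neither follows, because the error is in the conservative direction.
- **Secondary outcomes.** A reader might extend the criticism to the repeated-measures ANOVA. The article gives that method one sentence, and its silence on model terms is detail that an article commonly leaves to the full plan. It does not support a finding.
- **Condensation.** The article does not say that no other term will enter, and a separate plan may add site. This stands only in part: the section states the primary test, its covariate and the source of the intervals, and a model with site would differ from the one published.

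**Conclusion.** The mismatch between design and stated model is real; its consequence is conditional and modest. Assuming hospital explains 0 to 20% of residual variance, the reported standard error is 0 to 12% too large, and about 1 to 5% too large for a share of 2 to 10%. The true type I error lies between 5.0% and 2.8%. For 66 v 33 with 3.35 as the total residual SD, the power forgone is 0 to about 3 points (0.956 − 0.929 = 0.027 at the top of the range). It reaches about 4.5 points (0.906 − 0.861) only if 3.35 is a within-hospital SD and the hospitals differ by a full SD.

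These figures rest on an assumed ρ and on 198 evaluable patients balanced within hospital. The implied gaps in points and the within-hospital-SD case also assume equal-sized hospitals. This is a precision improvement available at almost no cost, and it does not threaten the trial's validity.

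**What to change.** Prespecify the primary ANCOVA with treatment, baseline WOMAC and hospital as a fixed factor, and take the confidence intervals from that model. The cost is one residual degree of freedom out of about 193 (198 patients less five parameters) and no new data, since hospital is known for every patient. Trial status says enrolment is still under way, so the term can be fixed before results are seen, which avoids a later choice between models. Carrying the site term into the models for the continuous secondary outcomes is an optional extension for consistency.
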